### Data collection

Questionnaires will be collected digitally and stored on a password-protected, secured server to which only study staff will have access. The physiotherapists will send the GAS scales, rehabilitation schemes and GAS scores to the research team by email and these will be stored at a locked location.

### Outcome measures

Table 1 provides an overview of the outcome measures of this study and the follow-up moments.

**Table 1 Tab1:** Overview of outcome measures collected at each time point

	Intervention group				Control group			
	Pre-operative	3 months	6 months	12 months	Preoperative	3 months	6 months	12 months
PROMs								
- VAS^a^	X	X	X	X	X	X	X	X
- KOOS	X	X	X	X	X	X	X	X
- OKS (-APQ)	X	X	X	X	X	X	X	X
- SQUASH	X	X	X	X	X	X	X	X
- WORQ	X	X	X	X	X	X	X	X
- HADS	X			X	X			X
- PAM	X			X	X			X
- NPS		X	X	X		X	X	X
- PT evaluation^b^		X	X	X		X	X	X
Performance measures								
- Activ8®	X		X		X		X	
- GAS scores	X	X	X					

^a^VAS concerning activities, primary outcome measure ^b^General questions on the delivery of physiotherapy

The primary outcome measure is a VAS for satisfaction concerning activities of daily life, work and leisure time including sports. The VAS is a validated, self-reported instrument that can accurately measure patient satisfaction on a scale ranging from 0 to 100, where zero is the worst score and 100 is the best score [19].


### Data and statistical analysis

Analyses will be performed according to the intention-to-treat principle. In our power analyses, we accounted for 15 % loss to follow-up. Reasons for loss to follow-up will be explored. Patients’ baseline characteristics will be inspected to assess comparability between the two groups. Descriptive statistics will be presented for each group as the mean change (standard deviation, 95 % confidence intervals) in both primary and secondary outcomes from baseline to each time point, using IBM**®** SPPS software, version 19.0.

For our primary outcome measure, the VAS for activities, both mean postoperative values and mean differences between preoperative and postoperative values between intervention- and control groups will be compared. Our main outcome is the VAS score at twelve months postoperatively. Mixed-model statistics will be used to take into account the effects of time and treatment. Outcome will be presented as improvement of intervention group compared to control group, including 95 % confidence intervals. In the case of a positive treatment effect, additional information for reaching clinically relevant differences will be presented, such as number needed to treat (NNT) and absolute benefit increase (ABI).

For the analysis of the secondary outcomes KOOS, OKS – APQ, SQUASH, WORQ, NPS, PAM and HADS, both mean postoperative values (at diverse follow-up moments) and mean differences between preoperative and postoperative values between intervention- and control groups will be compared. Mann-Whitney U tests will be performed to compare total scores of these questionnaires between intervention- and control groups at the specified follow-up moments, namely at three, six and twelve months postoperatively.

Activ8® activity monitor data will be presented as the total amount of minutes per day spent on each activity. Differences in activity level between intervention- and control group, measured preoperatively and six months postoperatively, will be calculated using Mann-Whitney U tests. Finally, we will report on the GAS scores collected at three and six months postoperatively. GAS scores will be considered ordinal data and non-parametric analysis methods will be used. We will present the percentage of patients reaching their goals (0) as well as the percentage of patients reaching less than their goal (-1), more than their goal (+1) and far more than their goal (+2) [37].

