Although the provision of postoperative physical therapy is almost universal, rehabilitation is the most understudied area concerning KA [15]. While short-term improvements of functional results with physiotherapy (PT) and exercise therapy after KA are shown in a recent systematic review, several aspects concerning rehabilitation after KA are unclear [16]. Recent surveys among physiotherapists showed that currently a great variety of PT methods is being used to attain patient goals in rehabilitation after KA [15, 17].

Considering the diverse expectations of this younger patient population on the one hand, and the importance of PT as part of rehabilitation on the other hand, the primary aim of the present study is to evaluate the effect of a multidisciplinary, goal attained and individualized rehabilitation on satisfaction of activities in daily life, work and leisure time including sports of younger patients (<65 years) after KA. The hypothesis is that multidisciplinary, goal attained and individualized rehabilitation, where patients’ goals are explicitly established and the feasibility of these goals is discussed and evaluated preoperatively, will result in higher patient satisfaction concerning these three domains compared to usual care physiotherapy rehabilitation.

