### Sample size

The primary outcome measure is a Visual Analogue Scale (VAS) for satisfaction regarding activities in daily life, work and leisure time, including sports. According to Singer et al. we use a minimal clinical relevant difference of ten points on a VAS scale from 0 to 100 with standard deviation of 15 [19]. Currently, data concerning how younger patients score satisfaction regarding activities in daily life, work and leisure time after KA are lacking. The best prediction can be extracted from the study of Kievit et al., in which young patients participating in a paid job with usual care after a KA scored a mean VAS score of 62 out of 100 points regarding work capacity [11]. According to these data, an intervention group has to score at least 72 (out of 100) points. Calculating with a power of 90 %, two-tailed testing with a *p*-value of 0.05, and standard deviation of 15 results in a minimum of 98 participants, 49 in the intervention group and 49 in the control group (nQuery Advisor® version 7.0). To adjust for 15 % dropouts over the 12 months follow-up period, 120 (60 per group) participants need to be included. It is expected that three patients per week can be included from the three locations of our hospital, so the inclusion period will cover approximately 40 weeks.

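### The plan makes the 12-month VAS score its main outcome but also compares change from baseline without ranking the two, so one deciding contrast should be fixed

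*Protocol article*

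**What the plan says.** **Outcome.** The Sample size section of the protocol article states: "The primary outcome measure is a Visual Analogue Scale (VAS) for satisfaction regarding activities in daily life, work and leisure time, including sports". Table 1 has one VAS row, collected preoperatively and at 3, 6 and 12 months in both groups.

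**Analysis.** For the primary outcome, the Data and statistical analysis section says that the groups will be compared on "the VAS for activities, both mean postoperative values and mean differences between preoperative and postoperative values". The next sentence names the VAS score at 12 months as the main outcome. Then comes: "Mixed-model statistics will be used to take into account the effects of time and treatment". The result is to be shown as improvement of the intervention group relative to control, with 95% confidence intervals. NNT and absolute benefit increase follow if the treatment effect is positive. The section does not say which comparison decides that.

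**Power.** The Sample size section uses a "minimal clinical relevant difference of ten points on a VAS scale from 0 to 100 with standard deviation of 15". Its control mean comes from a study in which working patients "scored a mean VAS score of 62 out of 100 points regarding work capacity", and the intervention target is 72. Both are postoperative levels, not changes.

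**The concern.** The postoperative mean and the pre-to-post difference are two statistics with different variances, and they can disagree in one data set. If the groups differ by chance at baseline, one may be significant and the other not. The article puts them side by side for the primary outcome and ranks neither in that sentence. The following sentence points to the 12-month score, but the word improvement can be read as change or as a between-group difference. A mixed model described by time and treatment could supply the 12-month difference, an effect averaged over visits, or a difference in change.

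This leaves room to choose the deciding comparison after seeing the data. That matters more here because, under Randomization and allocation concealment, participants, researchers and physiotherapists know the allocation, and the outcome is self-reported. The power statement also covers only the postoperative value. Whether it carries over to change depends on a correlation that the article does not give.

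**Working it through.** **Inputs.** From the Sample size section: difference 10, SD 15, two-sided 0.05, power 90%, 49 per arm. From Randomization and allocation concealment: 1:1 allocation. Assumed, because the article does not give them: the correlation *r* between baseline and 12-month VAS, taken as 0.2 to 0.7, and equal SDs of 15 at both times.

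**Step 1: the plan's own figure.** The article states: "value of 0.05, and standard deviation of 15 results in a minimum of 98 participants". The normal approximation is

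n per arm = 2 × (1.960 + 1.282)² × 15² / 10² = 47.3, so 48.

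The t-test version gives 48.26, so 49 per arm and 98 in total, which matches. Power at 49 per arm is 90.4%. With 120 enrolled and 15% lost, 120 × 0.85 = 102 remain, above 98. The sample size is right for a comparison of 12-month values.

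**Step 2: the same 49 per arm on other scales.**

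- Change score: SD = 15 × √(2(1 − r)). At r = 0.3 this is 15 × √1.4 = 17.75.
- 12-month value adjusted for baseline: SD = 15 × √(1 − r²). At r = 0.3 this is 15 × √0.91 = 14.31.

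| r | 12-month value: SD, power | Change: SD, power | Baseline-adjusted: SD, power |
|---|---|---|---|
| 0.2 | 15, 90.4% | 18.97, 73% | 14.70, 92% |
| 0.3 | 15, 90.4% | 17.75, 79% | 14.31, 93% |
| 0.5 | 15, 90.4% | 15.00, 90% | 12.99, 97% |
| 0.7 | 15, 90.4% | 11.62, 99% | 10.71, >99% |

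The change SD equals 15 when 2(1 − r) = 1, that is at r = 0.5. Below that the change comparison falls short of 90%; above it, it exceeds 90%. The number per arm for 90% power on change is 77, 68, 49 and 30 at r = 0.2, 0.3, 0.5 and 0.7. The baseline-adjusted comparison is at least as powerful as either alternative in every row.

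**Step 3: type I error if either comparison could count.** With equal SDs, the correlation between the two test statistics is √((1 − r)/2), for example √0.25 = 0.5 at r = 0.5. The bivariate normal probability that at least one is significant at 5% under no effect is 8.6% (r = 0.2), 8.8% (0.3), 9.1% (0.5) and 9.4% (0.7). So it is about 9% whatever r is in this range. It applies only under an either-counts rule, which the article does not state.

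**The case against.** A reader might infer that the plan has no single 5% test at all. The article does not support that. The sentence right after the two comparisons names the 12-month VAS score, a quantity and not just a visit. It agrees with the sample size, which sets 72 against 62 in one two-sided test. The two-comparison wording also recurs for the secondary outcomes, where the test is then named for total scores only. It may therefore describe what will be reported, not two primary tests. This part of the objection stands.

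A reader might also infer three primary tests, because the Background hypothesis is that the intervention "will result in higher patient satisfaction concerning these three domains compared to usual care physiotherapy rehabilitation". But the Sample size and Outcome measures sections, the analysis section and Table 1 all refer to one VAS. The hypothesis describes what satisfaction covers and does not define three endpoints, so no multiplicity across domains is counted here.

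A further objection is that model terms and covariates are commonly left to a statistical analysis plan, which is not shown. That is also right: their absence alone is no error, and the article's silence does not mean that baseline VAS will be ignored or that an average over visits is intended.

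What the objection does not remove is the stated text. Two between-group comparisons are listed for the primary outcome with no label on the second. The result is then expressed in a term that fits either one.

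**Conclusion.** The point holds in a limited form. The main outcome is designated, and the sample size is correct for it. What remains open is the status of the change comparison and which mixed-model contrast gives the primary result.

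The size is conditional. The 90% power carries over to change only if r is about 0.5 or more, and the article neither gives r nor points to data on it. An error rate near 9% is what an either-counts reading would cost, not what the plan prescribes. All power figures for change and for baseline adjustment assume equal SDs, complete data on 49 per arm and the assumed r; the baseline-adjusted figures are for the simple 12-month comparison.

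The reason to act is that one contrast removes the ambiguity and is no weaker than either listed comparison. At r = 0.3 power is about 93%, against 90% for the 12-month value and 79% for change.

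**What to change.** State one primary test: the between-group difference in the activities VAS at 12 months, two-sided 5%. Estimate it from the mixed model of the 3-, 6- and 12-month scores with treatment, visit, treatment-by-visit and baseline VAS as covariate, taking the treatment contrast at 12 months. Define improvement as that contrast, and make the NNT and absolute benefit increase conditional on it. Label unadjusted postoperative means, change scores and the 3- and 6-month comparisons as supportive.

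With baseline VAS in the model, the estimated treatment difference is the same whether the outcome is written as the score or as change from baseline, so the choice between the two disappears.

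The cost is wording only. The baseline VAS is already collected in both groups, and the 98 evaluable and 120 enrolled participants stand. The one thing given up is that a favourable change score can no longer be presented as the primary result. The change should be made before outcome data are examined by group.

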## Discussion

This paper provides the study protocol of the ACTION trial, which is a single-centre RCT that will investigate the effect of individualized, goal attained rehabilitation on patient satisfaction for activities of daily life, work and leisure time including sports after KA. The main goal of this study is to establish whether GAS is an effective rehabilitation method for achieving higher levels of patient satisfaction compared to usual care physiotherapy rehabilitation. With up to 20 % of patients remaining dissatisfied after KA, it is important to find new ways to further improve satisfaction in this patient group. Rehabilitation after KA plays a crucial role in helping patients to regain functionality and thereby improve participation. Although first described in 1968, GAS has gained renewed attention in recent years. It has shown promising results in several paediatric rehabilitation and neurorehabilitation studies and its use in these practices is growing [21, 37]. However, its use in rehabilitation after orthopaedic surgery has never been studied. As orthopaedic patient populations become more diverse, the need for individualized outcome measurements, such as GAS, increases. With our study we hope to provide a preliminary insight into the usefulness of GAS in orthopaedic rehabilitation settings. The proposed 6-point scale, ranging from -3 to +2 (compared to the original 5-point scale ranging from -2 to +2), allows us to also define and measure a possible relapse in a patient’s performance (-3) [38]. Since GAS is described at the activity and participation level of the ICF, we believe that the GAS goals will be highly relevant to the patient. The ICF intends to provide a standard language and conceptual framework for the description of health-related states [39]. By using the ICF framework, involved health professionals can communicate more effectively, since the same description is used universally. In this way, the practice variation that was observed in previous physiotherapy studies might be reduced, which is desirable because of the increasing demand for effectiveness (including cost-effectiveness) in healthcare. Furthermore, goals will be described in compliance with SMART (Specific, Measurable, Acceptable, Realistic and Time-specific) criteria [23]. These SMART goals are both relevant to the patient and considered acceptable and realistic by the physiotherapist and a multidisciplinary team consisting of orthopaedic surgeons, physiotherapists, orthopaedic researchers and human movement scientists. We expect that using this method will increase the chances of actually reaching a certain goal, whereby patients’ expectations will be met more often and patient satisfaction will increase. Since we expect to find enough eligible patients in our centre to complete inclusion within 40 weeks, we have chosen a single-centre study setting.

The primary strength of the proposed study is its multidisciplinary approach, with orthopaedic surgeons, physiotherapists, orthopaedic researchers and human movement scientists all involved in the study. In other words, the effect of a multidisciplinary approach in the treatment of young, active knee arthroplasty patients will be investigated. The second strength of this study is the broad range of patient-reported outcome measures (PROMs) and performance-based measures (Activ8, GAS scores) that will be collected, thus representing actual patient satisfaction and activities in the best possible way. The outcome measures are all relatively easy to collect and our aim is to gain complete data sets. When using PROMs, using a 12-month follow-up is suggested since clinically significant improvements still occur in the six-to-twelve month recovery period [40]. Therefore, with a follow-up of 12 months and a considerable difference between our two treatment groups in terms of the rehabilitation program, we expect to find a relevant difference in both patient-specific and performance-based outcome measures.

Our aim with the ACTION trial is to investigate whether a multidisciplinary, individualized rehabilitation can aid orthopaedic surgeons and physiotherapists in achieving higher patient satisfaction levels in their younger (<65 years) KA patient population. Furthermore, a first impression on the practical use of GAS in daily physiotherapy practice for orthopaedic patients can be obtained.

## Abbreviations

GAS: goal attainment scaling
KA: knee arthroplasty
OA: osteoarthritis
TKA: total knee arthroplasty
UKA: unicondylar knee arthroplasty
